**Blood and lymphatic system disorders**

Common: Eosinophilia, inhibition of thrombocyte aggregation (only when continuing infusion over a number of days).

**Metabolism and nutrition disorders**

Very rare: Hypokalaemia.

**Nervous system disorders**

Common: Headache.

**Cardiac disorders / vascular disorders**

Very common:

Increase of the heart rate by  $\geq 30$  beats/min.

Common: Blood pressure increase of  $\geq 50$  mmHg. Patients suffering from arterial hypertension are more likely to have a higher blood pressure increase.

Blood pressure decrease, ventricular dysrhythmia, dose-dependent ventricular extrasystole.

Increased ventricular frequency in patients with atrial fibrillation.

These patients should be digitalised prior to dobutamine infusion.

Vasoconstriction in particular in patients who have previously been treated with beta blockers.

Anginal pain, palpitations.

Uncommon: Ventricular tachycardia, ventricular fibrillation.

Very rare: Bradycardia, myocardial ischaemia, myocardial infarction, cardiac arrest.

Not known: Decrease in pulmonary capillary pressure.

Children: Pronounced increase of heart rate and/or blood pressure as well as a lower decrease of the pulmonary capillary pressure than adults. Increase of pulmonary capillary pressure in children under 1.

**Respiratory system, thoracic and mediastinal disorders**

Common: Bronchospasm, shortness of breath.

**Gastrointestinal disorders**

Common: Nausea.

**Skin and subcutaneous tissue disorders**

Common: Exanthema.

Very rare: Petechial bleeding.

**Musculoskeletal and connective tissue disorders**

Common: Chest pain.

**Renal and urinary disorders**

Common: Increased urgency at high dosages of infusion.

**General disorders and administration site conditions**

Common: Fever, phlebitis at the injection site.

In case of accidental paravenous infiltration, local inflammation may develop.

Very rare: Cutaneous necrosis

#### **Further undesirable effects**

Restlessness, nausea, headache, paraesthesia, tremor, urinary urgency, feeling of heat and anxiety, myoclonic spasm.

#### **2.4.2 Known Potential Benefits**

Dobutamine is a sympathetic amine that increases myocardial contractility through direct stimulation of myocardial adrenergic receptors. This pharmacodynamic effect has been exploited by neonatologists for several decades and was associated with long-term benefit in a study with an active comparator (dopamine) (30).

Dobutamine may have other effects that would be beneficial. These include systemic and pulmonary vasodilatation. Vasodilatation and reduced vascular resistance would lead to improved blood flow organ distribution. Increased stroke volume can be accomplished with no change or even decreased blood pressure due to the drug's potential vasodilatory effects (38).

Alternative therapies are in use. Dopamine is the most commonly used therapy and is under investigation in a parallel drug development plan.

Contrary to dopamine, dobutamine does not affect plasma catecholamine levels. In contrast to dopamine, no suppression of the hypothalamus-pituitary axis has been found after dobutamine treatment in neonates (27).

Dobutamine has been found to be more effective than dopamine in increasing systemic blood flow but not blood pressure in the immature preterm neonate during the first hours of extra-uterine life (28).

The use of a combination of biomarkers that have been proven to be as good predictors for adverse outcome will better define the population at risk of end-organ damage due to abnormal blood flow distribution that eventually would benefit from dobutamine treatment.

#### **2.4.3 Assessment of Potential Risks and Benefits**

The significant therapeutic benefits and fulfilment of therapeutic needs outweigh the risks involved. The existent literature supports the further development of dobutamine as a treatment for haemodynamic insufficiency in the 72 hours after birth in infants born at 32(+6) weeks gestation or below, as long as that evaluation is embedded in studies that carefully document information relating to safety, efficacy and dosing.

There is a favourable benefit-risk balance to support the evaluation of dobutamine in carefully monitored clinical studies. There is no risk related to proposed procedures included in this protocol.

#### **Efficacy:**

- Dobutamine has pharmacodynamic effects in several species from animal experimentation and in newborn humans that support the use of dobutamine to treat haemodynamic insufficiency during adaptation to preterm birth.
- There is preliminary evidence in human neonates with haemodynamic insufficiency that dobutamine has beneficial short-term effects.

- The indications for dobutamine remain unclear
- The optimal way to monitor the effects of dobutamine remains unclear
- The optimal dose and triggers for dose escalation remain unclear

**Safety:**

- A range of adverse events are associated with dobutamine use in adults. These do not preclude the use of dobutamine in that population
- The data from animal experimentation and newborn humans does not add significantly to the safety concerns.

Investigators are reminded of the need to collect data relating to both efficacy and safety in the clinical study. This will underpin a comprehensive assessment of the benefit/risk ratio in neonates at the conclusion of this programme.

A weight of evidence (WoE) approach, following the ICH S11 guideline, supports that this paediatric plan does not need further preclinical studies. Although the paediatric age group refers to neonates, therefore making further studies likely, the expected duration of the clinical intervention (treatment) is very low (less than 72 hours in more than 90% of treated infants)(35); and the indication is an acute condition (not a chronic use). These facts make highly improbable that such a short exposure to a pharmaceutical can eventually harm developing organ systems. The existing clinical data relevant for the intended study population come from the same age range, which supports additional safety profile. Risk mitigation strategies are also defined in the study protocol (see sections 6.1.3 Individual and Global Safety Parameters; 6.2.1 Rescue Treatment).

**3 OBJECTIVES AND ENDPOINTS**

| OBJECTIVES                                                                                                                                                                                                                              | ENDPOINTS                                                                                                                                                                                                                                                              |
|-----------------------------------------------------------------------------------------------------------------------------------------------------------------------------------------------------------------------------------------|------------------------------------------------------------------------------------------------------------------------------------------------------------------------------------------------------------------------------------------------------------------------|
| Primary                                                                                                                                                                                                                          | Primary                                                                                                                                                                                                                                                         |
| 
 
• To determine the minimum effective dose of dobutamine required to treat low SVC flow (<51 ml/k/min) in very preterm infants (short- term pharmacodynamic (PD) objective).
 
 | 
 
• Short-term PD endpoint: Minimum dobutamine dose to reach and maintain an SVC flow above 55 ml/k/min on an echocardiogram performed at 1 and 3 hours after effective infusion of the allocated dose [A].
 
 |
|                                                                                                                                                                                                                                         |                                                                                                                                                                                                                                                                        |

|                                                                                                                                                                                                                                                                                                                                                        |                                                                                                                                                                                                                                                                                                                                                                                         |
|--------------------------------------------------------------------------------------------------------------------------------------------------------------------------------------------------------------------------------------------------------------------------------------------------------------------------------------------------------|-----------------------------------------------------------------------------------------------------------------------------------------------------------------------------------------------------------------------------------------------------------------------------------------------------------------------------------------------------------------------------------------|
| Secondary                                                                                                                                                                                                                                                                                                                                       |                                                                                                                                                                                                                                                                                                                                                                                         |
| 
 
• To assess the proportion of infants who maintain an acceptable haemodynamic status with the dobutamine infusion alone in the first 72h from birth (efficacy).
 
• To evaluate the safety of dobutamine for the whole study population as well as for the seven treatment groups separately.
 
 | 
 
• Proportion of neonates achieving and maintaining a clinically acceptable haemodynamic status [B] with the dobutamine infusion alone in the first 72 hours from birth.
 
• Absolute and relative frequencies of adverse events (AEs) and severe adverse events (SAEs), to be recorded and compared between groups.
 
 |

|                                                                                                                                                               |                                                                                                                                                                                                                                                                                                                                                                                                                                                                                                                                                                                                                                                                                                                                                                                                                                                                                                                                                                                  |
|---------------------------------------------------------------------------------------------------------------------------------------------------------------|----------------------------------------------------------------------------------------------------------------------------------------------------------------------------------------------------------------------------------------------------------------------------------------------------------------------------------------------------------------------------------------------------------------------------------------------------------------------------------------------------------------------------------------------------------------------------------------------------------------------------------------------------------------------------------------------------------------------------------------------------------------------------------------------------------------------------------------------------------------------------------------------------------------------------------------------------------------------------------|
| 
 
To determine the individual variables that explain the interindividual pharmacokinetic (PK)/PD variability.
 
 | 
 
To determine the correlation between PK and PD.
 
 
[A] The effective start of the infusion (t0) will be calculated as the time at which the infusion pump is switched on plus the empirical value for the interval arising from the dead space. We summarize t0 as “the time at which dobutamine is expected to reach the circulation”
 
[B] Acceptable haemodynamic status is defined, for the purposes of this study, as the achievement and maintenance of dose success during the first 72 h from birth. The loss of such acceptable haemodynamic status occurs whenever there is a change in therapeutic strategy that involves cardiovascular treatment other than dobutamine alone due to exceeded safety parameters, treatment failure of the investigational infusion or the need for rescue treatment or death; any additional fluid bolus is considered as cardiovascular treatment.
 |
|---------------------------------------------------------------------------------------------------------------------------------------------------------------|----------------------------------------------------------------------------------------------------------------------------------------------------------------------------------------------------------------------------------------------------------------------------------------------------------------------------------------------------------------------------------------------------------------------------------------------------------------------------------------------------------------------------------------------------------------------------------------------------------------------------------------------------------------------------------------------------------------------------------------------------------------------------------------------------------------------------------------------------------------------------------------------------------------------------------------------------------------------------------|

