|                                                 | Pulse oximetry                                       | X*                     | X                  | X*                                               | X                                   | X*                        | X*                          | X              |                     |                                             |
|                                                 | Type of mechanical ventilation                       |                        | X                  | X                                                | X                                   | X                         | X                           | X              |                     |                                             |
|                                                 | Urine output                                         | X                      | X                  | X                                                | X                                   | X                         | X                           | X              |                     |                                             |
| primary outcome                                 |                                                      |                        |                    |                                                  | X                                   |                           |                             | X              |                     |                                             |
| Secondary outcomes                              |                                                      |                        |                    |                                                  |                                     |                           |                             |                | D                   |                                             |

X : Indicates Mandatory Procedures that should be entered into the eCRF;

X\*: Indicates data entered into the eCRF if available;

Pd\*: Indicates non-mandatory pharmacodynamics assessment at the visit that should be entered into the eCRF if available

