#### 6.1.2 Dosing and Administration

The study medication for infusion will be prepared and administered with strict standardisation of the administration system to minimise systematic errors due to differences in infusion set-ups. This will ensure the precise time at which dobutamine enters the body can be recorded (t0).

The infant's treatment will be guided by the responsible physician who will use the study medication under the premise of keeping a minimum time of 60 minutes from the effective infusion of dobutamine (t0) for PD assessment.

Once the primary PD variable has been assessed further management will be at the discretion of the attending physician. Therefore, if there is no PD response according to protocol with the allocated starting dose, or even if there were, the clinical situation of the patient so recommends it, the responsible physician decide on further treatment (Rescue treatment in section 6.2.1). However, clinicians are encouraged to consider the up-titration to maximum dobutamine dose first, to try to maintain the infant in the study drug as long as possible, if it is the best option for the infant.

Any changes to the treatment strategy will be documented by the responsible physician.

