### 6.1.3 Individual and Global Safety Parameters

In addition to rescue treatment in the absence of a clinical response to the study intervention, as described in section 6.4.1, the following safety parameters have been established to safeguard infants participating in the clinical trial.

A change of dose is allowed during the waiting time for clinical response, if any of the following **Individual Safety Parameters** are exceeded:

- Heart rate rises above 200 bpm.
- Mean blood pressure rises above pre-established values (Table 4)

**Table 4.** *Accepted upper limits of blood pressure according to GA and day of life*

|       | Day of life 1 |           |      | Day of life 2 |           |      | Day of life 3 |           |      |
|-------|---------------|-----------|------|---------------|-----------|------|---------------|-----------|------|
| GA    | Systolic      | Diastolic | Mean | Systolic      | Diastolic | mean | Systolic      | Diastolic | Mean |
| 24    | 46            | 33        | 37   |               |           |      |               |           |      |
| 26    | 50            | 35        | 40   |               |           |      |               |           |      |
| 28    | 55            | 37        | 43   |               |           |      |               |           |      |
| <28   |               |           |      | 50            | 36        | 41   | 52            | 37        | 42   |
| 30    | 58            | 39        | 45   |               |           |      |               |           |      |
| 32    | 60            | 41        | 47   |               |           |      |               |           |      |
| 33    | 63            | 43        | 49   |               |           |      |               |           |      |
| 28-32 |               |           |      | 61            | 44        | 50   | 65            | 45        | 52   |

In case of having a dose evaluation out of schedule (outside the 60 minutes intervals) due to a safety alert that triggers a dose modification, the infusion start time of the newly modified dose will be considered the 0 min time for a new 60 minutes dose evaluation.

The following **Global Safety Parameters** will also permit a change of dose during the waiting time for clinical response and may trigger a toxicity alert and halt of the trial in one or more clinical sites:

- Expected percentage of patient presenting safety issues:
  - Blood pressure above individual safety thresholds: < 20%

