#### *8.1.1.4 Treatment: PD/PK Assessment Visit*

The patient PD response to the dobutamine treatment should be evaluated at 60 minutes from the start of effective dose infusion, to establish if the treatment success dose has been achieved. Blood sample (1 millilitre) will be taken.

Effective dose infusion is define as the time ( $t_0$ ) when the study medication enters blood stream, which is calculated according to the following equation:

$$t_0 = t_{\text{switch on}} + t_d$$

$$t_d (\text{min}) = (\text{volume (ml)} / \text{velocity (ml/h)}) \times 60 (\text{min/h}),$$

where *volume* refers to the catheter lumen plus the stopcock dead space and *velocity* refers to the summation of the infusion rate of all the infusions coming through the line. Dobutamine infusion should be at the stopcock closest to the catheter entry. Before dobutamine is connected to the stopcock, the whole system (including bionector) will be fed with the dobutamine solution and the pump will be switched on for a few minutes to ensure that no pulling out effect is added at start. The pump will be switched off and the system will be connected to the stopcock. Finally the pump will be switched on and the time will be registered ( $t_{\text{switch on}}$ )

The following criteria will be checked at every patient at the dose evaluation:

- Main response biomarker: SVC flow > 55 ml/kg/min

And other parameters:

- MABP increase by 20% (roughly 4-6 mmHg)
- Decreasing serum lactate levels
- Base excess levels being less negative
- CRT < 4 sec

Throughout the treatment, a series of clinical and biochemical parameters described in sections 8.1.2 below are evaluated and recorded in the eCRF according to the timings given in the section 1.3.

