#### *8.1.1.5 Treatment: PD/ PK re-assessment Visit*

The patient PD response to the dobutamine treatment should be re-evaluated at 180 minutes from the start of infusion of the effective dobutamine dose (SVC flow above 55 ml /K/min). A second one millilitre of blood sample will be obtained.

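### The primary endpoint needs SVC flow above 55 at 1 h and 3 h on the allocated dose, but the visit text and Schedule score it at 60 minutes; the reading used can change the dose selected.

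*Protocol*

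**What the plan says.** The synopsis (section 1.1) and section 3 give the same primary endpoint: the minimum dose that reaches and maintains SVC flow above 55 ml/kg/min on an "echocardiogram performed at 1 and 3 hours after effective infusion of the allocated dose". Both time points and the allocated dose are part of it.

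The operational text differs:

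- **Section 8.1.1.4:** the response is "evaluated at 60 minutes from the start of effective dose infusion, to establish if the treatment success dose has been achieved".
- **Section 6.1.2:** the physician is bound to "keeping a minimum time of 60 minutes from the effective infusion of dobutamine (t0) for PD assessment". Then: "Once the primary PD variable has been assessed further management will be at the discretion of the attending physician". This applies to non-responders and, where the clinical situation calls for it, to responders.
- **Section 8.1.1.5:** the response is "re-evaluated at 180 minutes from the start of infusion of the effective dobutamine dose", and a parenthesis identifies that dose by SVC flow above 55. The synopsis entry on PK assessments accepts that the target effect may be reached on a dose other than the allocated one.
- **Section 6.1.3:** after a safety-driven change, "the infusion start time of the newly modified dose will be considered the 0 min time for a new 60 minutes dose evaluation".
- **Schedule of Assessments:** the row "primary outcome" is marked at the 60-minute visit and at 72 h. It is blank at the 180-minute visit.

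Section 6.1.1 and the synopsis say that the statistician learns the therapeutic response after each cohort of 3 and allocates the dose whose posterior success probability is closest to 80%. Neither gives the time point of that response or the dose it belongs to.

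**The concern.** A CRM attributes each success or failure to one dose level. If successes are counted at 60 minutes while the endpoint also requires 3 h, every infant who responds at 1 h and loses the response by 3 h is a success in the model and a failure on the endpoint. The success curve is then too high and the model settles on a dose that is too low for 80% success on the stated endpoint.

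Section 6.1.2 makes this likely in practice. It treats the primary variable as assessed after a minimum of 60 minutes and then allows the dose to change, so some infants will have no 3 h value on the allocated dose. No later analysis can recover it. The minimum effective dose is the trial's only primary deliverable, and the response is used during the trial after every 3 infants, so the definition has to be settled before enrolment.

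**Working it through.** **Inputs from the protocol (section 9.1.1):** success rates in the table of 45/70/80/90/95% at 5/7.5/10/12.5/15 microg/kg/min (steps 1 to 5), target 80%, maximum 30 infants. Cohorts of 3 come from section 6.1.1.

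**Assumptions, because the protocol does not state them:** one-parameter power model, normal prior with variance 1.34, start at step 1, no skipping of untried steps.

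**Step 1: reproduce the plan's own figure.** The table expects 5/9/12/4/0 infants per step (sum 30). With the table rates as truth, this model gives 3.4/8.4/13.2/4.9/0.1. Each cell is within 2 infants, so the model is a fair stand-in for the one used.

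**Step 2: relate the two scorings.** Let *r* be the share of 60-minute responders still above 55 at 3 h on the allocated dose. Then

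rate at 1 h and 3 h = *r* × rate at 60 min.

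Take the table as the truth on the stated endpoint, so that step 3 is the right answer at 80%. The 60-minute rates are the table rates divided by *r*, capped at 100%:

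| *r* | step 1 | step 2 | step 3 | step 4 | step 5 | closest to 80% |
|---|---|---|---|---|---|---|
| 1 | 45.0 | 70.0 | 80.0 | 90.0 | 95.0 | step 3 |
| 0.95 | 47.4 | 73.7 | 84.2 | 94.7 | 100 | step 3 |
| 0.90 | 50.0 | 77.8 | 88.9 | 100 | 100 (105.6 capped) | step 2 |
| 0.85 | 52.9 | 82.4 | 94.1 | 100 (105.9 capped) | 100 (111.8 capped) | step 2 |

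The switch occurs where steps 2 and 3 are equally far from 80%: (0.70 + 0.80)/(2*r*) = 0.80, so *r* = 0.75/0.80 = 0.9375. Losing more than about 6% of 60-minute responders by 3 h is enough.

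**Step 3: simulate the selected dose.**

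| Response fed to the CRM | step 2 | step 3 | step 4 |
|---|---|---|---|
| Stated endpoint (1 h and 3 h) | 22% | 57% | 20% |
| 60 min, *r* = 0.95 | 37% | 55% | 8% |
| 60 min, *r* = 0.90 | 56% | 41% | 1% |
| 60 min, *r* = 0.85 | 76% | 19% | 0% |

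Any remainder is almost all step 1. Repeat runs differ by a few percentage points.

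**Step 4: anchor the table at 60 minutes instead.** If the table rates are 60-minute rates, the stated endpoint has rates *r* × table. Steps 3 and 4 are then equally far from 80% at *r* = 0.80/0.85 = 0.941. At *r* = 0.90, a CRM fed the stated endpoint selects steps 2/3/4/5 in 6/39/51/4%, against 22/58/20/0% when fed 60-minute results. The direction is the same: at that retention, 60-minute scoring most often selects one step lower.

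**The case against.** The best defence is that the endpoint is written once, identically in the synopsis and section 3, and that sections 8.1.1.4 and 8.1.1.5 are its two stages: reach at 60 minutes, maintain at 180. The Schedule makes SVC flow mandatory at both visits. For an infant who responds at 60 minutes and stays on the allocated dose, the 180-minute echocardiogram is the same under either text. An infant below 55 at 60 minutes has already failed, so a missing 180-minute value does no harm there.

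That stands, and it limits the point: a reader might infer three rival endpoint definitions, but section 8.1.1.5 and the PK entry describe a visit and a sampling time. Neither says its result is the response sent to the statistician. Section 6.1.3 likewise restarts a bedside evaluation and is silent on model scoring.

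The defence does not explain why section 6.1.2 treats the primary variable as assessed before 3 h, or why the Schedule omits the primary outcome at 180 minutes and marks it at 72 h. Section 4.2 reports time to steady state from 15 to 180 minutes, so equivalence of the 60- and 180-minute results cannot be assumed.

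A reader might also infer that success after up-titration is credited to the allocated dose. No section says so, and section 6.1.2 speaks of response to the allocated starting dose. Were it done, selection would move down: with a share *u* of non-responders rescued and credited, steps 2 and 3 are equally far from 80% when 0.75 + 0.25*u* = 0.80, that is *u* = 0.20. This is hypothetical and carries no weight here.

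**Conclusion.** The contradiction holds and needs resolving before the first cohort is scored. Following the visit text and Schedule would score a different response from the stated primary endpoint, and nothing in sections 1.1 or 6.1.1 prevents that.

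Its effect on the dose is conditional. It would be tempting to say that the reading does change the dose declared minimum effective; the protocol supports only that it can. At 95% retention the 80% dose remains the most often selected (55% against 57%), although selection of the step below rises from 22% to 37%. At 90% the step below becomes the most likely choice (56% against 41%), and at 85% it dominates (76% against 19%). These figures rest on assumed retention, the assumed power model and prior, the table rates as truth, and 60-minute rates capped at 100% for the upper steps, which means constant retention cannot hold exactly there.

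**What to change.** Define the CRM response once and use it in sections 1.1, 3, 6.1.1, 6.1.2, 8.1.1.4 and 8.1.1.5: SVC flow above 55 ml/kg/min at both 60 and 180 minutes after t0 of the allocated dose, which is the endpoint already stated. Add that a response reached on another dose is not a success of the allocated dose, and state how an infant whose dose changes before 180 minutes is scored. In the Schedule, move the second primary-outcome mark from 72 h to the 180-minute visit; the 72 h assessment serves the secondary efficacy objective (section 8.1.1.6).

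This concerns scoring only. It prescribes no dose, titration or rescue rule, and it adds no condition on fluids or other drugs, which the protocol attaches only to the 72 h secondary endpoint. The cost is an amendment to wording and one Schedule row. Success rates will look somewhat lower than with 60-minute scoring, and each response will be known 2 h later.
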